**11.2 Source Documents and Access to Source Data/Documents**

The Investigator will maintain, and store in a secure manner, complete, accurate, and current study records throughout the study. In accordance with US regulations, the Investigator will retain all study records for at least two years following the date of marketing approval for the study products for the indications in which they were studied. If no marketing applications are filed, or if the applications are not approved, the records must be retained for two years after the FDA is notified that the INDs are discontinued. Study records include administrative documentation — including site registration documents and all reports and correspondence relating to the study — as well as documentation related to each participant screened and/or enrolled in the study — including informed consent forms, locator forms, case report forms, notations of all contacts with the participant, and all other source documents. All records must be retained on-site throughout the study’s period of performance. The investigator will allow inspection of all study-related documentation by authorized representatives of NIAID, Gilead Sciences, Inc and regulatory agencies to examine (and when required by applicable law, to copy) clinical records for the purposes of quality assurance reviews, audits, and evaluation of the study safety and progress. Study records will not be destroyed without approval from the NIH.

## 12.0 CLINICAL SITE MONITORING

On-site study monitoring will be performed in accordance with DAIDS policies. An independent study monitor will visit the site to:

- verify compliance with human subjects and other research regulations and guidelines
- assess adherence to the study protocol, study-specific procedures manual, and local counseling practices
- confirm the quality and accuracy of information collected at the study site and entered into the study database

Site investigators will allow a study monitor to inspect study facilities, the pharmacy and documentation (e.g. informed consent forms, clinic and laboratory records, other source documents, case report forms, drug accountability records), as well as observe the performance of study procedures. A site visit log will be maintained at the study site to document all visits.

## 13.0 HUMAN SUBJECTS PROTECTION

## 13.1 Institutional Review Board

## The protocol, informed consent forms, and recruitment materials, and other requested documents — and any subsequent modifications — will be reviewed and approved by the IRB at the MMC/AECOM. Subsequent to initial review and approval, the IRB will review the protocol at least annually. The PI will make safety and progress reports to the IRB and NIH at least annually, and within three months of study termination or completion. These reports will include the total number of participants enrolled in the study, the number of participants who completed the study, all changes in the research activity, and all unanticipated problems involving risks to human subjects or others.

## 13.2 Pre-enrollment Procedures

Prior to implementing the protocol and enrolling participants, a site must receive approval from DAIDS through the Regulatory Compliance Center (RCC) Protocol Registration Office. Subsequent amended protocols must also be approved by the RCC Protocol Registration Office. For complete instructions and required documentation for the protocol registration process, please refer to the DAIDS Protocol Registration Policy and Procedure Manual available on the RCC website at [http://rcc.tech-res.com](http://rcc.tech-res.com/). For questions concerning Protocol Registration, send an e-mail message to [[contact]](mailto:[contact]) or call [contact].

## 13.3 Informed Consent Process

Written informed consent will be obtained from each study participant before she is screened for the study. All participants also must verbally affirm their understanding of the investigational nature of the study, its risks and benefits, other treatment alternatives, their rights to terminate participation in the study without affecting their health care at the study site, whom to contact with questions regarding the study, and that he or she freely has given informed consent to participate in the study. A separate consent form will be obtained from each participant for HIV testing. Copies of the informed consent and HIV consent will be given to each participant and this fact will be documented in the participant’s record.

## 13.4 Participant Confidentiality

All study-related information will be stored securely at the study site. All participant information will be stored in locked file cabinets in areas with access limited to study staff. All laboratory specimens, reports, study data collection, process, and administrative forms will be identified by coded number only to maintain participant confidentiality. All computer entry and networking programs also will be done by coded number only, and all local databases will be secured with password-protected access systems. Forms, lists, logbooks, appointment books, and any other listings that link participant ID numbers to other identifying information will be stored in a separate, locked file in an area with limited access.

## Documentation, data and all other information generated will be held in strict confidence. No information concerning the study or the data will be released to any unauthorized third party, without prior written approval of the participant except as necessary for monitoring by the IRB, the Food and Drug Administration, the study sponsor, the OHRP, and the pharmaceutical supporters.

##

**13.5 Study Discontinuation**

Once a participant has enrolled in the study, the study site will make every reasonable effort to retain her for the complete study period. Given the relatively small study sample size, and the importance of ascertaining all outcomes among study participants, 100 percent retention of enrolled participants is targeted.

However, participants may withdraw from the study for any reason at any time. The Principal Investigator (PI) also may withdraw participants from the study in order to protect their safety and/or if they are unwilling or unable to comply with required study procedures.

During the study, participants with any abnormal condition will be treated according to standard clinical practice. A participant with a clinical toxicity outcome (see Appendix IV) who is discontinued from further product use will be considered to have reached a study endpoint. Participants also may be withdrawn if the study sponsor or regulatory authorities terminate the study prior to its planned end date.

Every reasonable effort will be made to complete a final evaluation of participants who terminate from the study prior to completion, and study staff will record the reason(s) for all withdrawals from the study in participants’ study records.

If at the screening or enrollment visits, a participant is found to have an abnormality on pelvic exam or a urinary tract infection, she will be ineligible to enroll in the study. Following treatment for candida vaginitis, bacterial vaginosis or urinary tract infection, she may be eligible to be re-screened for participation in the study. A minimum interval of one month is required between treatment and re-screening and all exclusion criteria will apply. If a participant is found to be pregnant, she will be referred for care.

Accrual into this study will be suspended if two or more participants experience similar grade 3 or higher AEs (as defined by the DAIDS Table for Grading Severity of Adverse Experiences) judged possibly, probably, or definitely related to product use. The protocol team in collaboration with the Safety Committee and NIH Medical Officer then will review all pertinent data and determine whether to continue accrual and product use. The team may decide to stop the study at this time, or at any such time that the team agrees that an unacceptable type and/or frequency of AEs have been observed.

The study also may be discontinued at any time by NIH, Gilead Sciences, Inc. and/or the FDA or other regulatory authorities.

**Appendix I. Schedule of assessments**

|  | **Screening** | **Enrollment**  **(Day 0)** | **Day 3** | **Day 7** | **Day 14** | **Final Visit (Day 21)** |
| --- | --- | --- | --- | --- | --- | --- |
| Informed Consent | X |  |  |  |  |  |
| Sexual History | X | X*b* | X*b* | X*b* | X*b* | X*b* |
| Medical History/Concomitant Meds | X | X*b* | X*b* | X*b* | X*b* | X*b* |
| HIV EIA | X |  |  |  |  |  |
| Provide HIV/STI pre-test counseling | X |  |  |  |  |  |
| Provide HIV/STI test results and post-test counseling |  | X |  |  |  |  |
| Urine Microscopy/Culture | X |  |  |  |  |  |
| Urine pregnancy test | X | X |  |  |  |  |
| Serum pregnancy test | X |  |  |  |  |  |
| Pelvic Exam | X | X | X | X | X | X |
| Bimanual examination | X |  |  |  |  |  |
| Pap smear*c* | X |  |  |  |  |  |
| Vaginal pH | X | X | X | X | X | X |
| Wet Mount (*Trichomonas*, *Candida*, BV) | X | X | X | X | X | X |
| Inspection for sperm on wet mount and PSA | X | X | X | X | X | X |
| Herpes simplex virus culture | X*a* | X*a* | X*a* | X*a* | X*a* | X*a* |
| *N. gonorrhoeae/C. trachomatis* | X | X*a* | X*a* | X*a* | X*a* | X*a* |
| Progesterone and Estradiol | X | X |  | X | X |  |
| Serum tenofovir level |  | X | X | X | X | X |
| Liver function tests (ALT, AST, total bilirubin, hep B surface ant, hep B core IgM, hep B core IgG ) | X |  |  |  |  |  |
| Kidney function tests | X |  |  |  |  |  |
| *T. pallidum* (RPR) | X |  |  |  |  |  |
| Herpes simplex virus serology | X |  |  |  |  |  |
| CVL collection | X | X | X | X | X | X |
| Record Adverse Events |  | X | X | X | X | X |
| Distribute study supplies |  | X |  |  |  |  |
| Distribute Participant Diary |  | X |  |  |  |  |
| Review Participant Diary |  |  | X | X | X | X |
| Count used & unused supplies |  |  | X | X | X |  |

*a*If clinically indicated

*b*Interim history collected

*c*A Pap smear will be obtained if documentation of a negative result within the last year is not available

**Appendix II. Laboratory Evaluations**

| **Test** | **Purpose** | **Specimen** | **Volume** | **Laboratory** |
| --- | --- | --- | --- | --- |
| HCG | Pregnancy | Urine | 10 ml | GCRC |
| Urine microscopy and culture | Urinary tract pathogens | Urine | 10 ml | MMC/AECOM |
| Wet mount | *Trichomonas*, *Candida*, BV, sperm | Swab/slide | n/a | GCRC |
| pH | Vaginal pH | Swab/pH paper | n/a | GCRC |
| PSA-specific antigen test | Semen detection | Swab | n/a | GCRC |
| GC/CT | *N. gonorrhoeae/ C. trachomatis* | Swab | 1 | MMC/AECOM |
| EIA with confirmation | HIV | Red Top | 5 ml | MMC/AECOM |
| RPR with confirmation | T. pallidum | Red Top | 3 ml | MMC/AECOM |
| Liver Function Tests & hepatitis serologies | Exclude liver disease | Red Top | 5 ml | MMC/AECOM |
| Kidney Function Tests | Exclude renal disease | Red Top | 2 ml | MMC/AECOM |
| Progesterone and Estradiol | Menstrual cycle phase | Red Top | 2 ml | MMC/AECOM |
| Serum HCG | Pregnancy test | Red Top | 2 ml | MMC/AECOM |
| HSV serology | HSV-1 & 2 Ab detection | Red Top | 3 ml | Investigator’s Lab |
| Pap smear | cancer screening | Slide | 1 | MMC/AECOM |
| Liquid chromatography | serum tenofovir level | Purple Top | 2 ml | Investigator Lab |
| FACS or immunohisto-chemistry | Inflammatory cells | CVL cell pellet | n/a | Investigator Lab |
| Liquid chromatography | CVL tenofovir level | CVL cell pellet | n/a | Investigator Lab |
| Liquid chromatography | CVL tenofovir level | CVL supernatant | 1 ml | Investigator Lab |
| Multiplex proteome array | Cytokines, chemokines | CVL supernatant | 3-5 ml | Investigator Lab |
| ELISA | SLPI, defensins, lactoferrin, IgG, IgA | CVL supernatant | 1 ml | Investigator Lab |

##

## Appendix III: Instructions for Using Tenofovir Gel

The study kit provided to you contains tubes of the study gel and applicators to insert the gel into the vagina. Before using the gel and applicators, please read the following instructions carefully. The study nurse will answer any questions you may have.

1. Remove one applicator and one tube of study gel from the study kit.

2. Remove applicator from the sealed wrapper. Before filling the applicator, push plunger completely down inside barrel.

3. To open the tube, unscrew the plastic cap. Turn the cap upside down and puncture the foil seal on the opening of the tube.

4. Holding the tube upright, attach the applicator barrel to the neck of the tube and turn the applicator clockwise until it is firmly seated.

5. Hold the applicator firmly on the tube neck. Squeeze the tube from the bottom filling the applicator to the single line indicated.

6. Unscrew the study gel tube from the applicator.

7. With one hand, hold the filled applicator by placing your thumb and middle finger HALF-WAY along the barrel.

8. Choose a comfortable position, for example, standing with one leg raised, squatting with your feet apart, or lying on your back with your knees apart. With the other hand, gently spread the vaginal opening.

9. GENTLY slide the applicator into the vagina until your fingers touch your body. Be careful not to insert the applicator too far.

10. Hold the applicator firmly in place and push the plunger into the barrel (the gel-filled half of the applicator). With the plunger still depressed, withdraw the applicator from the vagina.

11. Replace plastic cap on study gel tube and store the used tube in the study kit. Bring the study kit with you on your next visit. Store in an area not accessible to children. Product should be stored at controlled room temperature until required for administration. Controlled room temperature is defined as 25 degrees Celsius (°C)/ 77 degrees Fahrenheit (°F).

12. Used applicators should be stored in the study kit and should be brought with you to each visit.

## Appendix IV: Outcomes, Diagnostics, and Follow-Up Procedures

Individual participants may withdraw from study participation at any time, for any reason, without loss of other benefits or services to which they may be entitled. Participants with any abnormal condition will be treated according to standard clinical practice.

| **Condition** | **Product Use** | **Evaluation** | | **Enrollment Action** | | **Follow-up and Treatment Action** | |
| --- | --- | --- | --- | --- | --- | --- | --- |
| Ulceration | Adverse clinical event, discontinue product use | Culture for genital herpes. |  | | Re-evaluate in 5 to 7 days. If the ulcer has become worse or not healed in 5 to 7 days, perform a biopsy. Ask the participant to return in 7 to 10 days for follow-up. | |  |
| Abrasion | Continue |  |  | | Re-evaluate by speculum examination in 48 to 72 hours. If the condition is worse, discontinue product use. If the condition is the same, continue product use. | |  |
| Generalized erythema or severe edema: A localized area of more than 30% of vulvar surface or combined vaginal and cervical surface affected by erythema | Adverse clinical event, discontinue product use |  |  | | Re-evaluate in 5 to 7 days. | |  |
| Vaginitis | Adverse clinical event, discontinue product use | Perform wet mount for *candida vaginitis, trichomoniasis,* and bacterial vaginosis. |  | | Manage with oral medication and re-evaluate in seven days. If resolved, restart product use. If the participant has asymptomatic candida vaginitis at the Day 7 visit she should continue product use and be re-evaluated at the Day 14 visit.[[1]](#footnote-2) | |  |

| Suspected cervicitis | Provisionally continue | Evaluate for *N. gonorrhoeae and C. trachomatis*. Perform wet mount for  *trichomoniasis.* | If laboratory results confirm pathogen, discontinue treatment. | Treat with oral medication and re-evaluate in 5 to 7 days. |
| --- | --- | --- | --- | --- |
| Petechial hemorrhage | Continue |  |  | Re-evaluate by speculum examination in 48 to 72 hours. If the condition is worse, discontinue product use. If the condition is the same, continue product use. |
| Ecchymosis | Continue |  |  | Re-evaluate by speculum examination in 48 to 72 hours. If the condition is worse, discontinue product use. If the condition is the same, continue product use. |
| Sub-epithelial hemorrhage with swelling | Continue |  |  | Re-evaluate by speculum examination in 48 to 72 hours. If the condition is worse, discontinue product use. If the condition is the same, continue product use. |
| Mild to moderate erythema or edema: A localized area of less than 30% of vulvar surface or combined vaginal and cervical surface | Continue |  |  | Re-evaluate by speculum examination in 48 to 72 hours. If the condition is worse, discontinue product use. If the condition remains the same, continue product use. |
|  |  |  |  |  |

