## Follow-up Visit (Day 14)

A subsequent visit will be scheduled after 12-15 days of product dosing (target Day 14). Every attempt will be made to schedule appointment after 14 days of dosing to ensure adequate exposure. If a participant has discolored or malodorous vaginal discharge or suspected cervicitis at any Study Visit, an appropriate clinical and laboratory work-up will be conducted (see Appendix IV). If a participant has a genital ulcer, tests will be conducted for syphilis or herpes simplex as appropriate. Continuation in the study will be based on the severity of the abnormality noted as described in Appendix IV.

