## 9.0 CLINICAL MANAGEMENT

**9.1 Toxicity Management**

In response to AEs reported by study participants and/or observed upon exam by study staff, the study site investigator or designee will recommend either continuation or holding gel use consistent with the criteria in Appendix IV. Product use also will be held or discontinued in the event of a expedited adverse event (EAE) that is judged by the site Investigator or designee to be definitely, probably, possibly, or probably not related to the study gel or applicator.

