**9.6 Criteria for Permanent Treatment Discontinuation for an Individual Participant**

The criteria for permanent treatment discontinuation of further study product/intervention(s) for an individual participant are:

- Treatment-related toxicity (see section 9), including pelvic inflammatory disease, deep epithelial disruption
- Requirement for prohibited concomitant medications such as oral antibiotics
- Pregnancy or breastfeeding
- Completion of treatment as defined in the protocol
- Request by participant to terminate treatment
- Clinical reasons believed life-threatening by the physician even if not addressed in the toxicity section of the protocol
- Unwillingness or inability to remain abstinent for the duration of the study.

The participant will continue to be followed with participant’s permission if study product/intervention (s) is discontinued.

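### Appendix IV, section 9.6 and section 6.5 conflict on product use when cervicitis or vaginitis needs oral treatment, and the cervicitis row is incomplete

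*Protocol*

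**What the plan says.** **Appendix IV, suspected cervicitis.** The product-use entry is "Provisionally continue". The evaluation is for gonorrhoea, chlamydia and trichomonas. The only stopping instruction is "If laboratory results confirm pathogen, discontinue treatment", and the follow-up entry is "Treat with oral medication and re-evaluate in 5 to 7 days".

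**Appendix IV, vaginitis.** Product is stopped, the condition is managed orally and reviewed at seven days, and product resumes if it has cleared.

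**Appendix IV, rows that continue product** (abrasion, petechial hemorrhage, ecchymosis, sub-epithelial hemorrhage, erythema or edema under 30%). Each carries the step "Re-evaluate by speculum examination in 48 to 72 hours. If the condition is worse, discontinue product use".

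**Section 9.6.** The criteria for permanent product discontinuation include "Requirement for prohibited concomitant medications such as oral antibiotics" and, separately, "Treatment-related toxicity (see section 9), including pelvic inflammatory disease, deep epithelial disruption".

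**Section 6.5.** All concomitant medications are allowed except vaginal products. Oral antibiotics are not mentioned.

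**Section 7.1, Day 3, 7 and 14 visits.** After naming suspected cervicitis and pointing to Appendix IV, each says: "Continuation in the study will be based on the severity of the abnormality noted as described in Appendix IV".

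**Section 9.1.** The investigator "will recommend either continuation or holding gel use consistent with the criteria in Appendix IV".

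**Section 6.4.** A participant taken off product for an Appendix IV toxicity outcome counts as having reached a study endpoint and is not replaced.

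**The concern.** A site clinician treating cervicitis or vaginitis during the dosing period has at least three places to look for the product decision, and they do not agree. The cervicitis row is also silent in the situation that the introduction treats as the central safety question, inflammation of the mucosa caused by the product itself: tests are negative, or the finding is worse at review.

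Two things are at stake. One is consistent handling of participants in a first look at mucosal safety. The other is the data: whether a woman is recorded as a toxicity endpoint, and whether she goes on contributing on-product samples, depends on which section the clinician applied.

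**Working it through.** The plan states no figure on this point, so the check sets the passages side by side. The only arithmetic is dose counting.

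**1. Cervicitis treated with an oral antibiotic.** The row speaks of oral medication, not antibiotics. Appendix V, however, gives a course of oral antibiotics as its example of therapy for Grade 2 cervicitis, so the case can arise. The row does not limit oral treatment to women with a positive test.

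- Pathogen confirmed: Appendix IV stops product and 9.6 stops it permanently. They agree on stopping, though the row does not say whether the stop is permanent.
- No pathogen: Appendix IV leaves the woman on product, while 9.6 stops it permanently. The decisions are opposite.
- Section 6.5 puts no restriction on the antibiotic in either case, although 9.6 calls it prohibited. The nearest support for 9.6 is the exclusion in 5.2 for oral antibiotics in the past 7 days, which that section's lead-in extends to any time during participation.

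**2. Vaginitis treated with an oral antibiotic.** Appendix V names oral antibiotics and antifungals for Grade 2 vulvovaginitis. For an antibiotic, Appendix IV allows product to resume after resolution and 9.6 makes the stop permanent. For an antifungal, 9.6 does not clearly apply.

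**3. What the cervicitis row leaves out.** A confirmed pathogen is its single stop trigger. It states no action for a negative result and none for a worse or unchanged finding at review. All five other rows that continue product have a stop-if-worse step. The visit text points to a severity criterion in Appendix IV, but this row has none. Appendix V grades cervicitis, yet no product action is attached to those grades.

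**4. Overlap with the erythema rows.** Appendix V lists erythema among cervicitis findings. Erythema above 30% of the combined vaginal and cervical surface means stopping product, and below 30% it means a review at 48 to 72 hours. The cervicitis row gives a different action and interval. No rule says which row prevails.

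**5. Timing.** Daily dosing gives 14 doses on Days 0 to 13, with visit-day doses taken after the visit.

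- Found on Day 7: review falls on Day 7 + 5 = 12 to Day 7 + 7 = 14. The remaining doses are those of Days 7 to 13, that is 7. Doses taken before review: Days 7–11 = 5, up to Days 7–13 = 7.
- Found on Day 3: the row's review would fall on Day 8 to 10, but the scheduled Day 7 speculum examination normally comes first, after the doses of Days 3–6 = 4.
- For comparison, a review at 48 to 72 hours follows 2 to 3 doses.

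These counts assume that no pathogen result or other rule stops product first.

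**6. Endpoint classification.** Under 6.4, a discontinuation through Appendix IV is an endpoint without replacement. Through the cervicitis row, a woman with a confirmed infection could therefore count as a toxicity endpoint, while a woman with pathogen-negative cervicitis would not. With 12 women per arm, one classification is 1/12 = 8.3% of an arm.

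**The case against.** The strongest reply is that the cervicitis row can be read in sequence: continue provisionally, test, stop if a pathogen is found, then treat. On that reading oral treatment goes only to women already off product, and the row agrees with 9.6. The reading is possible, but the text does not state it, and the treatment entry carries no condition. It also does nothing for the vaginitis row, where resuming product after oral treatment is explicit. The placement of the stop sentence within the table may be an effect of text extraction and is given no weight here.

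A reader might infer something stronger: that cervicitis caused by the gel stays on product at any severity. The documents do not support that. Section 9.6 stops product for treatment-related toxicity, and its examples are not exhaustive. Section 9.1 holds or stops product for an expedited adverse event judged anywhere from definitely to probably not related. The ulceration row and the row for erythema above 30% stop product whatever the test result. Section 13.5 lets the investigator withdraw a participant for her safety. These routes are real, but they do not complete the row: the toxicity criterion in 9.6 refers back to section 9, 9.1 refers back to Appendix IV, and the expedited-event route covers only such events.

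It is also fair to say that the visit sentence on severity defers to Appendix IV. It is a cross-reference without a target in this row, not a competing rule. Falling under two rows of a management table is ordinary as well; the difficulty is only that no precedence is given.

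**Conclusion.** The concern holds as an inconsistency among Appendix IV, 9.6 and 6.5, together with an incomplete cervicitis row. It is not a finding that the protocol as a whole lacks a way to stop product for gel-induced cervicitis. For a woman with pathogen-negative cervicitis who is given an oral antibiotic, two sections followed literally lead to opposite product decisions. For vaginitis treated with an oral antibiotic, one section allows resumption and another forbids it.

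The exposure at issue is up to 5 to 7 of the 7 remaining doses for cervicitis found on Day 7, and about 4 doses before the next scheduled examination if found on Day 3. The conclusion assumes that the oral medication in Appendix IV can be an antibiotic, which Appendix V supports, and that dosing and visits fall on target days. The documents give no rate of cervicitis or vaginitis, so the number of women affected cannot be estimated. The point merits correction because it bears on safety and endpoint counting and is cheap to settle.

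**What to change.** Reconcile the cervicitis, vaginitis and erythema rows of Appendix IV, the severity sentence in the Day 3, 7 and 14 visit text of section 7.1, section 9.6 and section 6.5, checking 5.2 at the same time. After reconciliation the text should give one product action for each of these cases:

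- a participant who needs oral treatment, stating whether the oral medication in Appendix IV is the oral antibiotic of 9.6;
- a pathogen-negative result in suspected cervicitis;
- the finding at re-evaluation;
- a participant who meets more than one row.

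It should also say which of these discontinuations count as the toxicity endpoint of 6.4. Which action applies in each case is for the sponsor's clinicians to decide.

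The cost is an amendment to a few table rows and cross-references. The reconciliation itself requires no added visit, test or participant.
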